## Abstract

Previous studies of multiple languages have found processing differences between patient-first and agent-first word orders. However, the results are inconsistent as they do not identify a specific ERP component as a unique correlate of thematic role processing. Furthermore, these studies generally confound word order with frequency, as patient-first structures tend to be infrequent in the languages that have been investigated. There is evidence that frequency at the sentence level plays a significant role in language processing. To address this potential confounding variable, we will test a language where the non-canonical sentences are more frequent and are comparable to the canonical sentences, namely Standard Indonesian. In this language, there is evidence from acquisition, corpus, and clinical data indicates that the use of passive is frequent and salient. One instance of this difference can be demonstrated by the fact that it has been suggested that frequency may be the reason why Indonesian-speaking aphasic speakers do not have impairments in the comprehension of passives, whereas speakers of other languages with aphasia often do. In the present study, we will test 50 native speakers of Indonesian using 100 sentences (50 active and 50 passive sentences). If the neural correlates of thematic role processing are not observed in the critical region of the sentence (the prefix of the verb), this would suggest that the previous results were indeed influenced by frequency, but if we find that specific ERPs are connected to the hypothesized syntactic operations, this would further reinforce the existing evidence of the increased cognitive load required to process more syntactically complicated sentences.

## Introduction

For most individuals, understanding sentences is an effortless, uneventful process. However, early research has suggested that not all sentences are equal. Consider the passive structure: Compared to active sentences, passives are acquired and used later by children [1],take longer to process, and are prone to misinterpretation by adults [2]; they also pose difficulties for individuals with brain lesions [3].Debates regarding how humans process different types of sentences have evolved over time. The use of event-related potentials (ERPs) to study language processing is commonplace not only among language researchers, but also among psychologists and clinicians.

In recent years, the vast number of studies investigating neural responses during language processing have mainly focused on linguistic anomalies. The utilization of these violations has yielded distinct ERP responses. The P600, for example, is seen in response to syntactic violations such as violating the expected word order [4] or inflection [5], reflecting semantic integration [6],and the processing of long-distance wh-dependencies [7]. Other ERPs, such as the N400, appear as a result of anomalies such as semantic incongruence [8], the integration of the overall sentence meaning [9], or memory retrieval [6].

### Word order processing in ERP research

While the study of ERP responses to linguistic anomalies has been valuable, the tested structures are, by their own nature, anomalies which seldom appear in normal language use [10]. This leads to the question of whether the neural responses that are found in reaction to anomalies can also be observed during typical language comprehension. Not only is there less research on the topic of processing of typical sentences compared to studies using violation-paradigms in sentence processing, which might be considered surprising given that this is the type of language that individuals encounter in daily communication, but the few studies that exist have found little to no consistency and have been plagued by potentially confounding variables such as syntactic frequency. This subsection will discuss the studies that focused on word order effects in sentence processing.

Some studies have documented differences in the processing of different word orders, such as between subject and object relative clauses [10, 11], as well as of simple sentences such as the subject-object and the object-subject word order distinction in German [12]. Most of these studies have investigated languages with a canonical subject-first word order, either SOV or SVO, and have reached similar conclusions: Object-first structures require more effort to process than subject-first structures. For example, in the sentence with an object-embedded relative clause (1a), “The man” is not the agent of the first verb, thereby this does not adhere to the typical English word order in which the agent is placed in the first position [13]. This results in a predicted increase in syntactic processing demand (as reflected in reaction times or accuracy rates, see [2]). The sentence with a subject-embedded relative clause (1b), however, does not violate this expectation, as the NP1 of the sentence is the agent of the action.

1a) The man who the woman violently scolded, admitted the error.1b) The man who violently scolded the woman, admitted the error.

Matzke et al. [12] compared object-before-subject (OS) to subject-before-object (SO) structures in German with the provision of case information through the use of articles. The temporary ambiguity of case information was also included as a factor by using feminine case markers on the article (*die*) of the NP1 which, in German, can signify both the accusative and the nominative case (2 and 3).

2) Object—Subject

Die begabte Sängerin entdeckte der talentierte Gitarrist.

*The gifted singer*_*(Fem*. *Nom/Acc*.*)*_
*discovered the talented guitar player*_*(Masc*.*Nom*.*)*_.

‘The talented guitar player discovered the gifted singer.’ [Ambiguous until ‘der’]

3) Subject—Object

Die begabte Sängerin entdeckte den talentierte Gitarrist.

*The gifted singer*_*(Fem*. *Nom*.*/Acc*.*)*_
*discovered the talented guitar player*_*(Masc*.*Acc*.*)*_.

‘The gifted singer discovered the talented guitar player.’ [Ambiguous until ‘den’]

In the masculine NP1 sentences, with regard to the Object-Subject compared to the Subject-Object structures in German, Matzke et al. [12] found a Left Anterior Negativity (LAN) for the critical time window (NP1) that continued for the rest of the sentence. Left fronto-temporal negativity was observed following the 2^nd^ article in the Object-Subject condition. In the condition that was ambiguous up to the second article (as in examples 2 and 3), a P600 was found in the disambiguation section (the 2^nd^ article ‘der’) of the Object-Subject compared to the Subject-Object structures. Matzke et al. [12] attributed the initial LAN on the NP1 to working memory. In a similar experiment, Schlesewsky, Bornkessel, and Frisch [14] found that the LAN was only observed in object-first non-pronominal NP1s in German, and not in pronominal NP1s (as shown in example 4).

4) Object-first pronominal structure

Gestern    hat    ihn    der Vater    dem Sohn    gegeben.

Yesterday    has    it_ACC_    the_NOM_ father the_DAT_ son    given

‘Yesterday, the father had given it to the son’.

As such, the authors came to the conclusion that the LAN originates from a local syntactic mismatch via the violation of canonicity principles in non-pronominal NP1s, rather than from higher working memory usage due to dislocated objects in general.

Other studies which have investigated thematic role assignment processing through ERPs included Meltzer and Braun [10], who compared the processing difference between subject-embedded and object-embedded relative clauses in English, and they found a negativity at NP1 (400-800ms) and a positive shift at the offset of the relative clause for reversible clauses. Jackson, Lorimor, & van Hell [15] observed positivity at the 500-700ms time window when comparing English passive structures to active structures; this positivity was strongest at the left anterior electrodes. In a study of Japanese, Wolff, Schlesewsky, Hirotani, and Bornkessel-Schlesewsky [16] included sentences that were similar to those in German, in which the object-first structures were compared to subject-first structures via the use of a suffix in the nominative or accusative case on the NP. ERPs for object-initial compared to subject-initial structures after NP1 included an early (120-240ms) negativity, which was referred to as ‘scrambling negativity’, a broadly distributed positive shift at the NP1 of Object-Subject structures (400-650ms), an N400 at the NP2 for Subject-Object structures, and a late parietal negativity (650-1050ms) at the verb. Aside from the object scrambling, the positive shift at the NP1 in object-initial sentences was interpreted as the resolution of dependency introduced by an accusative-first argument. Another study on Japanese [17] investigated how context usage influences processing of object-first structures. They observed that object-first structures elicited a sustained LAN at NP1 and P600 at NP2 when the NP1 was new and not provided in the context.

A similar late parietal negativity at the verb was reported in Japanese in another study that used scrambled sentences [18]. A study on simple declarative sentences in Basque [19], which marks NPs with the ergative and absolutive cases, showed a similar negativity post-onset of the NP1 of object-first sentences. Like in Japanese, the NP2 follows the NP1 in Basque, with the verb in the final position. In the NP2 position, a left negativity (400-550ms) for object-first structures was found. In the P600 time window (700-900ms) in the verb position, a parietal positivity was observed. The negativity at the NP1 for object-first structures, although observed in a different time window, is suggested to be related to the scrambling negativity found in both German and Japanese. The effect at the NP2 is interpreted as a LAN that expresses working memory usage for displaced elements, or, alternatively, Erdocia et al. [19] suggested that subjects and objects are processed differently regardless of their position. They hypothesized that the P600 observed at the verb position for object-first structures relates to an increase of processing costs when elements are displaced from their canonical positions. These studies attributed the late negativity to general increased processing of scrambled sentences.

For case-marking languages, there appears to be a pattern of a negative shift in NP1, which is the critical region of the sentence for thematic role assignment. However, other parts of the sentence indicate a different pattern: The P600 found in both Basque [19] and English [15] verbs is somewhat contradictory, as the case information denoting the thematic role assignment was provided earlier at the NP1 in Basque; as such, this P600 cannot be attributed to thematic role processing, and the authors attributed it to ‘higher syntactic complexity’. By contrast, a study of Japanese [16] found a late negativity on the verb, which was an effect in a similar time window but with opposite polarity. Due to the inconsistencies in these findings (which may be in part attributed to the experimental design and the languages examined in these studies), it is particularly difficult to draw a conclusion on what constitutes a neural correlate of thematic role processing. To summarize the findings of comparable studies, Table 1 outlines the results of the discussed literature with results from [10] presented separately as unlike the other studies, they discuss relative clauses with different regions measured.

**Table 1 pone.0272207.t001:** Summary of previous ERP studies comparing word orders.

Language	Conditions	NP1	NP2	V	Note
German* [12]	SVO-OVS	LAN (400-600ms, 600-800ms)	- Negativity (400-1000ms)	Not discussed	Nom/Acc case was provided by articles preceding NPs.
	Ambiguity (fem. NP1 vs masc. NP1)		- P600 (600-800ms, 800-1000ms) for amb. fem. NP1		
Japanese* [16]	SOV-OSV	- Scrambling negativity (120-240ms)	N400 (300-500ms)	Late negativity (650-1000ms)	Nom/Acc case was provided by markers following the NPs.
		- positivity (400-650ms)			
Basque* [19]	SOV-OSV	Negativity (300-500ms)	Negativity (400-550ms)	P600 (700-900ms)	Erg/Abs case was provided by markers following the NPs.
English* [15]	Act-Pas	Not discussed	Not discussed	P600 (500-700ms)	Frontal distribution of P600- different from the typical distribution in garden-path sentences.
	Conditions	NP1	RC onset	RC offset	
English [10]	S.RC–O.RC	Negativity (400-800ms) for reversible	Not found	positivity (-300-100ms)	Only found reversibility effects, no word order effect.
	Reversibility	(i.e. ani. NP1 vs inani. NP1)		for rev. conditions	

*all components are evoked to compare object-first to subject-first structures

### Some relevant properties of Standard Indonesian

Indonesian is a zero-marking language [20] without case or gender markings. Transitive verbs are usually only inflected for voice (active or passive), and there is no verb inflection for tense, aspect, or agreement. Indonesian has SVO word order [21]; however, the ordering of constituents can be flexible, and it is possible (although infrequent) for verbs to take the initial position. Chung [22] suggested that Indonesian belongs to a branch of the Austronesian language family that was originally verb-initial, as the passivized transitive, active-transitive, as well as intransitive verbs can take the 1^st^ position.

The usual transitive passive (5b) has the patient in the initial position. Examples of typical simple active and simple passive sentences are as follows:

5a) Simple active (agent-patient / SVO)
Perempuan    itu    **men**dorong    laki-laki    itugirl    the    **ACT**-push    boy    the‘the girl is pushing the boy’5b) Simple passive (patient-agent / OVS)
Laki-laki    itu    **di**dorong    (oleh) perempuan    ituboy    the    **PAS**-push    (by)    girl    the‘the boy is pushed by the girl’

The canonical sentence (5a) contains a verb with an active-transitive voice marking (*men-*). Likewise, the passive is expressed by the prefix (*di-*) on the verb in (5b), where ‘the boy’ is the patient of the action. Similar to English, the by-phrase is optional in the passive. In addition, the preposition (*oleh*) ‘by’ may be omitted when the agent is immediately adjacent to the verb (Cole & Hermon, 2008). As the current study observes the ERP distinctions between the simple active and the simple passive, it is also worth noting that the typical passive in Indonesian, unlike in most Indo-European languages, is highly frequent. It is acquired at a very early stage (around 2 years old; [23]) compared to English (4–5 years old), which can be attributed to its high input frequency of 28–35% in Indonesian, compared to 4–5% in English. This difference is also reflected in the written form: Only 9% of English verbs display passive morphology [24] compared to 30–40% of Indonesian verbs [25] having the passive marker ‘*di-*‘.

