### The present study

The current study will investigate the processing of non-anomalous, simple sentences with differing word orders. The focus will be on the critical point in time, which is mainly the verb, but other regions of the sentence (such as NP2) will be investigated to check for spill-over effects.

The two conditions to be included are the active and the passive. The materials will be typical, plausible, reversible (both noun phrases are animate), violation-free sentences. There are some aspects of the Indonesian language that make the topic of the present study worth pursuing. First, the thematic roles of the NPs are coded by the passivization prefix on the verb rather than by case marking on the NPs. Second, unlike the studies of German [12] and Basque [19], no ambiguity manipulations are involved. Third, the structures to be tested in the current study are both relatively frequent compared to the passive structures in previously studied languages and are considered to be typical. The object-first conditions in the previous studies are infrequent in the respective languages compared to their subject-first counterparts; for example, the object-embedded relative clause in English [26] and the object-subject structure in German [27] are both highly infrequent structures. While arguments against exclusively syntactic frequency-based accounts of sentence processing have been established for German [28], there is behavioral evidence of the influence of sentence-level frequency and its interaction with other syntactic contrasts, such as the lexical bias of verbs [29–31].

The current experiment will contribute by providing electrophysiological data from Standard Indonesian, a zero-marking language that lacks many morphosyntactic features of Indo-European languages, paired with a relatively rigid word order. To the best of our knowledge, no ERP study has investigated Indonesian, where the ‘non-canonical’ sentence structure is relatively frequent. This is important because all the previous studies have compared one common sentence structure to an extremely infrequent one, and there is a wealth of evidence suggesting that syntactic frequency plays a role in sentence processing at the behavioral level [2, 32, 33].

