### Materials

Participants will read stimuli comprising 100 semantically reversible active and passive sentences (see S1 Appendix in S1 File). Examples of which are shown in Table 2.

**Table 2 pone.0272207.t002:** Stimuli examples of each condition.

Condition	NP1	Art	VP	Adjunct	NP2	PP/RC
Active	Polisi	itu	menembak	langsung	seorang perampok	di malam hari.
	Police	that/the	**ACT**shoot	immediately	(a) robber	at night.
		(the/a) police immediately shoots (the/a) robber at night.				
Passive	Polisi	itu	ditembak	langsung	oleh perampok	di malam hari.
	Police	that/the	**PAS**shoot	immediately	by robber	at night
		(the/a) police is immediately shot by (the/a) robber at night				

The sentences involve an animate subject and object and are constructed while avoiding a plausibility bias. Word order is manipulated by using two structures: simple active and simple passive sentences. Based on previous studies on processing well-formed sentences, the contrast of interest is passive-active, and whether the effects of the word order persist. We will strive for active-passive pairing plausibility with the use of NP1 and NP2 that are plausibly reversible (i.e. each sentence should not be strongly biased to one interpretation due to the nouns used). Additionally, there will be 200 filler trials consisting of questions (e.g. What did the adventurer notice yesterday?) and cleft sentences (e.g. it is the boy who the girl is calling) to prevent the habituation of the participants. The task for both the experimental and filler sentences will be discussed in the Procedure. The stimuli will be tested for acceptability and prototypicality using an online survey method utilizing a Likert scale of 1 to 7 with a similar setup used by Jackson, Lorimor, & van Hell [15]. Assuming the materials are rated acceptable and plausible by raters, the materials will not be further edited.

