## Predictions

There are several possible patterns of the results. These are described below.

An ERP contrast can be expected between canonical and non-canonical sentences on the critical region (verb). We can expect a posterior positivity (P600) at the disambiguation point to indicate that a revision of the thematic information is needed: NP1 should be reassigned from the default agent role to become the patient of the action.An ERP contrast can be expected between canonical and non-canonical sentences in the NP2 time windows. Additionally, based on earlier studies we expect a ‘generalized’ increase in processing costs in comprehending the non-canonical structures attributed to violation of transitivity expectation [16] as well as retrieval of verbal material in a non-canonical position and uptick in working memory demands [19]. For example, the verbs in Basque [19] and Japanese [16] provide no additional thematic information, but within that section, ERP differences for object-first compared to subject-first structures were observed.A lack of ERP correlates in both the verb and NP2, especially between the passive and active conditions, suggests that previous findings regarding the neural correlates of thematic role assignment were confounded by syntactic frequency because the studies compared one highly frequent structure (e.g. active) to a highly infrequent sentence structure (e.g. passive).

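### The frequency evidence covers the verb but not the overt *oleh* agent at NP2, yet the Predictions make the frequency conclusion depend on NP2 as well

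*Protocol article*

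**What the plan says.** All references are to the protocol article.

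- **Some relevant properties of Standard Indonesian.** The written figure is a count of verbs by prefix: "compared to 30–40% of Indonesian verbs [25] having the passive marker" *di-*. A second figure refers to "its high input frequency of 28–35% in Indonesian, compared to 4–5% in English", with no counting unit stated. The same section says "Similar to English, the by-phrase is optional in the passive", and that the preposition "by’ may be omitted when the agent is immediately adjacent to the verb".
- **The present study.** The claim is about structures: "the structures to be tested in the current study are both relatively frequent compared to the passive structures in previously studied languages". The verb is the main region, and NP2 is examined for spill-over.
- **Materials, Table 2.** The example passive has an adjunct after the verb and then "oleh perampok" as NP2. The example active has the same adjunct and then *seorang perampok*.
- **Frequency, and Table 3.** Control is by token frequency or frequency class of the active and passive verb forms. The section concedes that manipulating structural frequency may not be feasible.
- **Predictions.** An NP2 contrast is tied to a generalised processing cost of non-canonical structures, with a passive negativity expected at 300–600 ms. The frequency conclusion is tied to "A lack of ERP correlates in both the verb and NP2".
- **Abstract.** The same inference is tied to the verb prefix only.

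**The concern.** The stated aim is to remove frequency as an explanation of passive–active differences. That works only in regions where the frequency evidence describes what the reader is processing. At the verb it does: the reader has NP1, *itu* and a prefixed verb, and counts of prefixed verbs are the relevant measure. At NP2 the reader meets an agent phrase that many passives may not have. Nothing in the article shows how common that continuation is after a *di-* verb, or how common an object is after a *men-* verb.

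If the *oleh* agent is the less expected continuation, a passive–active difference at NP2 may be a frequency effect. The Predictions would report it as a cost of word order and, because the rule asks for a null in both regions, would also withhold the conclusion that frequency explains earlier results. The confound the study sets out to remove would return in one of its two tested regions.

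**Working it through.** **1. Checking the article's own figures.** The 30–40% and 28–35% come from cited sources and cannot be rebuilt from the document. Table 3 can be checked:

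- active range 124627 − 301 = 124326, as stated;
- passive range 342595 − 411 = 342184, as stated;
- ratio of means, passive to active, 26415.88 / 21513.1 = 1.23.

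The verb-form control is therefore internally sound and, on the means, slightly favours the passive. It is a count of word forms and says nothing about what follows them.

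**2. What is measured against what is read.**

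| Region | What the reader has seen (Table 2 passive) | Frequency evidence in the article |
|---|---|---|
| Verb | NP1 + *itu* + *di-* verb | *di-* share of verbs; verb-form counts |
| NP2 | the above + adjunct + *oleh* agent | none for this continuation |

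**3. How far the missing quantity could matter.** Let *s* be the share of *di-* passives with an overt *oleh* agent. The article does not give *s*; the values below are assumptions.

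Share of written verbs = (30% to 40%) × *s*

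| *s* | Share of written verbs |
|---|---|
| 0.10 | 3–4% |
| 0.25 | 7.5–10% |
| 0.50 | 15–20% |
| 0.75 | 22.5–30% |
| 1.00 | 30–40% |

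The cited figure fixes the structure's frequency only at *s* = 1, which would mean that the optional phrase is always present.

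**4. A second difference at NP2.** In the example item the NP2 noun is the same, but the first word is *oleh* in the passive and *seorang* in the active. Words appear for 500 ms with a 100 ms blank, so the next word starts at 500 + 100 = 600 ms. If the NP2 trigger sits on the first word of the NP2 column, the predicted 300–600 ms window ends as the noun appears. For an item built like the example, that window compares responses to two different words.

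**5. Which outcomes are affected.**

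| Verb | NP2 | Reading under the Predictions | Effect of this point |
|---|---|---|---|
| null | null | earlier findings confounded by frequency | none; the joint null is not made easier |
| null | difference | generalised cost; frequency conclusion withheld | the difference may come from the continuation or the first word, so the conclusion may be withheld wrongly |
| difference | null | revision of thematic roles at the verb | none |
| difference | difference | as above, plus generalised cost | the verb reading stands; the NP2 reading is not identified |

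**The case against.** **The main region is untouched.** This stands. The Abstract ties the null inference to the verb prefix, and The present study describes NP2 as a spill-over check. But the Predictions put NP2 into the decision rule and give it a directional hypothesis, so the article does not hold to that role. A reader might infer that frequency control fails throughout; the documents do not support that.

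**The tested passive might be as rare as the English passive.** A reader might infer this from the low rows of the sensitivity table. It does not follow. The English written figure ("Only 9% of English verbs display passive morphology") also counts all passives, and the by-phrase is optional there too. Discounting only the Indonesian figure is not like-for-like. With the same *s* in both languages the ratio does not change: 30/9 to 40/9, about 3.3 to 4.4. The article's cross-language claim is relative, and this point does not overturn it.

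**The adjunct is in both conditions.** This stands. The adjunct does not narrow the passive alone; only the overt agent is specific to it.

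**The evidence on the stimuli is thin.** This stands in part. Table 2 shows one item per condition and the full list is in an appendix not shown, so it cannot be said that every passive has this form or that every NP2 begins with different words. The 28–35% is attached to the typical passive, and the article's own example of one has an agent, so that figure may not need discounting.

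**The stimuli will be rated for acceptability and prototypicality.** Ratings bear on whether the sentences are odd. They do not measure how often one continuation follows a verb form.

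**Conclusion.** The point holds for NP2 and only there. The frequency evidence describes the verb, while the decision rule in the Predictions also uses a region it does not describe. The outcome at risk is a null at the verb with a difference at NP2, where the frequency conclusion could be withheld for a reason unrelated to word order. Wherever NP2 differs, attributing the difference to non-canonical order is not supported.

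No magnitude can be stated, because the share of *di-* passives with an *oleh* agent is not given; the assumed values span 3–4% to 30–40% of written verbs. The conclusion does not need a low value, only that the quantity is unmeasured and the phrase optional. It also rests on the Table 2 items being representative of the stimuli. The inference rule should be changed before data collection; the design need not be.

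**What to change.** In Predictions:

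1. Base the frequency inference on the verb contrast alone, in line with the Abstract and The present study.
2. Describe NP2 as a spill-over analysis that is not frequency-controlled, and remove it from the condition for the frequency conclusion.
3. State that an NP2 passive–active difference cannot be attributed to word order rather than to the frequency of the agent continuation or to the NP2-initial word.

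Optionally, report beside Table 3, from the corpus already in use, how often the chosen *di-* forms are followed by an *oleh* agent and the *men-* forms by an object. This should be descriptive. Comparable counts would not make NP2 frequency-controlled in the sense the study wants, because the first word still differs between conditions in the example item.

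**Cost.** The wording change needs no new participants, stimuli or recordings. The optional count takes some work: *oleh* can be searched for directly, but finding objects after *men-* forms requires identifying noun phrases. The real price is that the NP2 result supports a narrower claim.
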